## Abstract

**Background:**

Mental illnesses represent a significant global health challenge, affecting millions with far-reaching social and economic impacts. Traditional exercise prescriptions for mental health often adopt a one-size-fits-all approach, which overlooks individual variations in mental and physical health. Recent advancements in artificial intelligence (AI) offer an opportunity to tailor these interventions more effectively.

**Objective:**

This study aims to develop and evaluate a multimodal data-driven AI system for personalized exercise prescriptions, targeting individuals with mental illnesses. By leveraging AI, the study seeks to overcome the limitations of conventional exercise regimens and improve adherence and mental health outcomes.

**Methods:**

The study is conducted in two phases. Initially, 1,000 participants will be recruited for AI model training and testing, with 800 forming the training set, augmented by 9,200 simulated samples generated by ChatGPT, and 200 as the testing set. Data annotation will be performed by experienced physicians from the Department of Mental Health at Guangdong Second Provincial General Hospital. Subsequently, a randomized controlled trial (RCT) with 40 participants will be conducted to compare the AI-driven exercise prescriptions against standard care. Assessments will be scheduled at 6, 12, and 18 months to evaluate cognitive, physical, and psychological outcomes.

**Expected outcomes:**

The AI-driven system is expected to demonstrate greater effectiveness in improving mental health outcomes compared to standard exercise prescriptions. Personalized exercise regimens, informed by comprehensive data analysis, are anticipated to enhance participant adherence and overall mental well-being. These outcomes could signify a paradigm shift in exercise prescription for mental health, paving the way for more personalized and effective treatment modalities.

**Registration and ethical approval:**

This is approved by Human Experimental Ethics Inspection of Guangzhou Sport University, and the registration is under review by ChiCTR.

## Introduction

1

Mental illnesses, a significant global health concern, encompass a wide spectrum of psychological disorders affecting millions worldwide (1, 2). The ramifications of these disorders extend beyond the individual, affecting families, communities, and economies. For instance, depression alone is a leading cause of disability worldwide, and mental disorders are among the major contributors to the overall global burden of disease (3, 4). The societal impact of mental illness is profound, encompassing economic costs due to lost productivity, healthcare expenses, and the intangible yet substantial cost of reduced quality of life (5, 6). Additionally, mental health disorders can exacerbate social issues such as homelessness and unemployment, creating a vicious cycle of poverty and illness (7).

The field of exercise prescription for mental illness has garnered increasing attention in recent years, as evidenced by a growing body of research. Studies have consistently demonstrated the efficacy of regular physical activity in alleviating symptoms of various mental disorders, including depression, anxiety, and schizophrenia (8–11). For example, a meta-analysis by Rosenbaum et al. indicated that moderate to vigorous physical activity could significantly reduce depressive symptoms in adults (12). Despite these advancements, several challenges and gaps remain in the application of exercise prescription for mental health. A primary concern is the lack of individualization in exercise regimes. Most existing studies and protocols adopt a one-size-fits-all approach, neglecting the unique needs, preferences, and limitations of individual patients (13). This generalized approach may lead to suboptimal outcomes and lower adherence rates, as patients may find the prescribed exercises either too challenging or not engaging enough. Another significant limitation is the scarcity of data-driven methods in tailoring exercise prescriptions. While some studies have begun to explore the use of data in optimizing exercise interventions (14, 15), there is still a considerable gap in integrating comprehensive, multimodal data – such as genetic, physiological, and behavioral information – to inform exercise prescriptions. This lack of integration results in missed opportunities to enhance the precision and effectiveness of exercise as a therapeutic tool for mental health.

The integration of Artificial Intelligence (AI) in healthcare and medicine has marked a transformative era, particularly with the advancements in deep learning algorithms and the enhanced capabilities in processing large volumes of data (16, 17). These technological leaps have enabled the deployment of AI across various medical fields, including mental health, internal medicine, infectious disease control, heart failure management, and diabetes care, among others. Specifically in the domain of mental health (18), AI-driven tools are being used to predict patient outcomes, personalize treatment plans, and even assist in early diagnosis through pattern recognition in patient data. In internal medicine (19), AI algorithms contribute to diagnostic accuracy and patient management, while in the field of infectious diseases control (20), AI plays a pivotal role in outbreak prediction, tracking, and formulating response strategies. The application of AI is equally significant in managing chronic diseases. For instance, in heart failure (21, 22), AI assists in patient monitoring, risk assessment, and tailoring treatment regimes. Similarly, in diabetes management (23), AI technologies are employed for continuous glucose monitoring and predicting episodes of hypoglycemia or hyperglycemia, thereby enhancing patient care. In the context of China’s medical resource constraints, the development of AI-based prescription recommendation systems is particularly promising (24). These systems have the potential to mitigate the gap in healthcare delivery, offering efficient, accurate, and accessible medical advice. A notable example of such innovation is the reinforcement learning-based dynamic prescription recommendation system proposed by Wang and colleagues (25). This system exemplifies the application of AI in optimizing treatment plans, adapting to patient-specific needs and changes over time (26).

In the burgeoning field of exercise prescription, the application of AI and machine learning has begun to show promising results. Tuka and Linhart have explored the potential of these technologies for creating personalized exercise prescriptions, tailoring recommendations to the unique needs and conditions of patients (27). Additionally, this research underscores the superiority of current AI technology over traditional methods in exercise prescription. AI systems offer a higher degree of personalization and adaptability, leveraging real-time data to tailor exercise plans more effectively to individual needs and conditions. This approach signifies a significant shift from traditional, generalized exercise guidelines to more individualized, data-driven strategies.

In a more targeted study, Chen and colleagues have devised a hierarchical learning framework specifically designed for crafting physical exercise prescriptions for Chinese children (28). This innovative framework takes into account various factors such as age, physical development, and individual health conditions, demonstrating the effectiveness of AI in addressing the diverse needs of specific populations. However, despite these advancements, there remains a notable gap in the literature regarding the application of machine learning in the context of exercise prescription for mental health. Mental illness presents unique challenges and necessitates tailored approaches in exercise prescription, considering factors like psychological state, medication side effects, and the fluctuating nature of symptoms. To bridge this gap, our research aims to develop an interpretable, machine learning-based intelligent system dedicated to exercise prescription for the prevention and management of mental illness. This system will not only adapt to the individual needs of patients but also provide insights into the rationale behind each prescription, ensuring transparency and trust in AI-driven recommendations.

## Methods

2

### Study design

2.1

In the first phase, we focus on developing a multimodal data-driven intelligent system for exercise prescription. To achieve this, we will initially recruit 1,000 participants for AI model training and testing. Of these, 80% (800 participants) form the training set. To enhance the robustness and generalizability of the AI model, we will use ChatGPT to simulate an additional 9,200 cases based on the initial 800, resulting in a comprehensive training set of 10,000 instances. The remaining 20% (200 participants) will be reserved as a testing set. This diverse dataset will then be annotated by a team of 10 experienced doctors from the Department of Mental Health at Guangdong Second Provincial General Hospital. Their expertise will ensures the accuracy and clinical relevance of the data labeling, which is critical for the development of a reliable and effective AI system.

In our analysis, we will set the effect size at 0.5 to assess the intervention’s effectiveness. This value represents a medium effect size, which is considered substantial in the context of our study. Following the development and preliminary testing of the AI model, the second phase of the study will involves an RCT with 50 participants. These participants are randomly divided into two groups: 25 in the experimental group and 25 in the control group. The experimental group will receives personalized exercise prescriptions generated by the newly developed AI system, while the control group will receives standard exercise recommendations. This phase aims to evaluate the efficacy of the AI-driven exercise prescription system in a real-world clinical setting. The RCT’s design ensures that the results are robust and can be attributed specifically to the intervention, thereby providing strong evidence of the system’s potential benefits for individuals with mental illnesses.

The effectiveness of the AI-driven exercise prescriptions is evaluated at multiple time points: initially at the end of the 6 months trial period (Trial Completion Assessment), followed by a 6 months follow-up assessment and a 12 months follow-up assessment. These assessments are designed to track and compare the short-term and long-term impacts of the AI-driven exercise prescriptions on the mental health outcomes of the participants (shown in Figure 1).

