### Data annotation

3.2

In the crucial phase of data annotation, our study collaborates with the Department of Mental Health at Guangdong Second Provincial General Hospital, enlisting the expertise of five experienced physicians. The data annotation process involved five doctors, each with over 10 years of experience. The dataset was divided equally among them, with each doctor responsible for annotating a specific portion. This approach ensured that the entire dataset was annotated efficiently and effectively, with all doctors completing their assigned tasks until the full dataset was annotated.

The physicians, utilizing their medical expertise and understanding of mental health, carefully review the responses from the various questionnaires, including the STAI, CES-D, and others. The doctors consider several critical aspects of exercise prescription: (1) Type of Exercise: determining the most suitable form of physical activity, whether it’s aerobic, strength training, flexibility exercises, or a combination, based on the participant’s health status and preferences; (2) Frequency: establishing how often the participant should engage in the prescribed exercises, balancing effectiveness with practicality. (3) Intensity: setting the appropriate level of exertion for each exercise, tailored to the individual’s physical capabilities and mental health needs. (4) Duration: recommending the length of each exercise session to maximize benefits while ensuring safety and adherence.

The initial dataset comprised 800 cases, designated as the training set, and a smaller set of 200 cases, set aside as the test dataset. To augment the robustness and diversity of our training dataset, we employed the *ChatGPT* to generate an additional 9,200 simulated samples. This step was based on the patterns and characteristics observed in the initial 800 cases. By doing so, we significantly expanded our dataset, enriching the training process and enhancing the model’s ability to generalize across a broader range of scenarios. This extensive data annotation and augmentation process is crucial for developing an accurate and effective AI-driven exercise prescription system. It ensures that the model is not only trained on a substantial and varied dataset but also fine-tuned to reflect real-world complexities and nuances in mental health and physical fitness.

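### Simulated cases make up 92% of the training records, no model is fitted on the real cases alone, and the text does not settle who labels the simulated cases

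*Protocol article*

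**What the plan says.** All of this is in the protocol article.

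- **Real cases.** Section 2.1: "we will initially recruit 1,000 participants for AI model training and testing". The split follows: "Of these, 80% (800 participants) form the training set" and "The remaining 20% (200 participants) will be reserved as a testing set". Section 3.2 agrees that the test cases are kept apart: "a smaller set of 200 cases, set aside as the test dataset".
- **Simulated cases.** Section 2.1: "we will use ChatGPT to simulate an additional 9,200 cases based on the initial 800, resulting in a comprehensive training set of 10,000 instances". The stated purpose is a more robust and more general model. Section 3.2 repeats the 9,200 and treats the benefit as obtained.
- **Annotators.** Section 2.1 has the data "annotated by a team of 10 experienced doctors". Section 3.2 describes "enlisting the expertise of five experienced physicians".
- **Allocation of reading.** Section 3.2: "The dataset was divided equally among them, with each doctor responsible for annotating a specific portion". No overlap between portions is described.
- **Order.** Section 2.1 sets out the augmented training set and the test set and only then says that the dataset will be annotated. Section 3.2 describes annotation of the questionnaires first and simulation from the 800 cases afterwards.
- **Selection.** Section 3.3 lists seven model types, trains them on the annotated data, and picks the one that does best on the testing set. It anticipates an AUC above 0.9.

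**The concern.** The simulated records add no new patients. They restate, through a language model, what 800 people contributed. They may help the fit or they may distort the link between questionnaire responses and prescription. The plan asserts the first and includes no comparison that could tell the two apart.

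It also matters who supplies the labels. If doctors label the simulated cases, the model learns physicians' judgement about artificial patients. If ChatGPT supplies them, most of the training labels are not physicians' judgements at all. These are different studies, and the article does not settle which is planned.

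The selected model writes the prescriptions for the intervention arm of the randomised trial (sections 2.1 and 4.2). A weakness in training therefore passes directly into the treatment being tested.

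**Working it through.** **1. The plan's own figures reproduce.** Inputs are from section 2.1.
- 1,000 × 0.80 = 800 training cases; 1,000 × 0.20 = 200 test cases.
- 800 + 9,200 = 10,000 training records.

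**2. Share of simulated records.**
- 9,200 / 10,000 = 0.92, or 92%.
- 9,200 / 800 = 11.5 simulated records per real one.
- Independent people contributing to training: still 800.

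**3. What the annotation contradiction implies.** Records to be read are 1,000 if only real cases are labelled, and 10,000 + 200 = 10,200 if simulated cases are labelled too.

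| Cases read by doctors | Five doctors (section 3.2) | Ten doctors (section 2.1) |
|---|---|---|
| 1,000 real | 1,000 / 5 = 200 each | 1,000 / 10 = 100 each |
| 10,200 real and simulated | 10,200 / 5 = 2,040 each | 10,200 / 10 = 1,020 each |

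The possible workload runs from 100 to 2,040 cases per doctor, about a twentyfold range (2,040 / 100 = 20.4).

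**4. What the 200 real test cases can show.** For accuracy p, the 95% half-width is 1.96 × √(p(1 − p)/200).
- p = 0.9: 0.042
- p = 0.8: 0.055
- p = 0.7: 0.064

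For an AUC A = 0.9, the Hanley-McNeil standard error is √{[A(1 − A) + (m − 1)(a − A²) + (n − 1)(b − A²)]/(mn)}, with a = A/(2 − A), b = 2A²/(1 + A), m positives and n = 200 − m negatives. The class split is not given, so it is assumed over a range. The 95% half-widths (1.96 × SE) are:
- m = 100: 0.044
- m = 50: 0.059
- m = 20: 0.092

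A large loss of performance on real people would be visible.

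**5. What choosing the model on the same 200 cases does.** Suppose all seven model types have the same true accuracy p and make independent errors. The expected maximum of seven binomial proportions on 200 cases, minus p, was simulated with 200,000 repetitions.
- p = 0.9: 0.028
- p = 0.8: 0.038
- p = 0.7: 0.043

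These are upper values. Models tested on the same people make correlated errors, which reduces the optimism.

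**6. What the 200 cases cannot show.** Every candidate that reaches them has been trained on the mixture. With no real-only counterpart, the contribution of the simulated records cannot be separated from the choice of algorithm, the quality of the labels or the difficulty of the task. The test labels come from the same single-reader process, so a habit of one doctor can appear in both training and test labels.

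**The case against.** The strongest defence is the test set. It holds 200 recruited participants, is not augmented, and every candidate is tested on it. A reader might infer from the 92% share that the model could learn artefacts which nothing in the plan would detect. The documents do not support that: step 4 of the working shows that the test set is precise enough to reveal a large loss. What remains is that it cannot attribute the loss, and that it serves for both selection and reporting.

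Three further inferences also go too far.

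- That simulated cases carry 92% of the weight in fitting. The figure is a share of records. No weighting is stated, and influence on the fit depends on the algorithm.
- That every case has exactly one doctor's label. This holds for the cases that doctors read. Whether they read the simulated ones is the open question.
- That differences between doctors cannot be separated from differences between cases. The article does not say how portions are assigned. With random assignment, 100 to 200 real cases per doctor would allow average differences to be estimated. What single reading does lose is agreement on the same case.

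It can also be said that an article condenses a fuller plan, which may hold a real-only comparison and agreement statistics. That is fair, and their absence alone would not be a finding. But the two annotator numbers, the two orders of work and selection on the testing set are stated, and condensing does not explain the contradictions.

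**Conclusion.** The point holds as a cheap improvement together with an inconsistency to reconcile. It does not show that the model will fail.

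- **Certain from the text:** 92% of training records are simulated from 800 people; no fit on the real cases alone is described, although a benefit is claimed; annotators number ten in one section and five in another; the two sections order annotation and simulation differently; the test set also selects the model.
- **Conditional:** the 3 to 4 point optimism is an upper range. It assumes seven equally good models with independent errors and true accuracy between 0.7 and 0.9. The AUC half-widths of 0.04 to 0.09 assume between 100 and 20 positives among the 200.
- **Unknown:** whether the simulated cases help or harm. The documents give no figure for this, and the plan as described would not produce one.

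**What to change.** 1. Before any simulation, set aside a real validation subset of the 800 and generate simulated cases only from the remaining real ones. Alternatively, repeat the simulation inside each cross-validation fold. Ordinary cross-validation within the 800 after simulating from all 800 would not do: the held-out cases would already have shaped the simulated records, which favours keeping them.
2. Fit each of the seven candidates with and without the simulated cases (7 × 2 = 14 fits per split). Choose the model, and decide whether to keep the simulated cases, on the held-out real cases. Then refit.
3. Use the 200 test cases once, for the final performance report.
4. Reconcile the number of annotators and the order of annotation and simulation, and state who labels the simulated cases.
5. Assign cases to doctors at random, so that average differences between doctors can be estimated.

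The cost is extra computing, simulation repeated once per fold if folds are used, and fewer real cases for fitting during selection. If doctors label simulated cases, each new simulated set needs labelling as well; a single validation subset keeps that burden lowest. No extra participants are needed.

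Optionally, a second doctor could read a sample independently to measure case-level agreement. Reading all 200 test cases again would take 200 / 5 = 40 readings per doctor with five doctors, or 200 / 10 = 20 with ten. This costs reader time, and the main fix does not depend on it.

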### RCT design and methods

4.1

Our study employs a parallel-group RCT to evaluate the effectiveness of an AI-based exercise prescription system in mental health management. Participants are divided into two groups: an intervention group and a control group, each consisting of 25 individuals. This balanced design allows for a robust comparison of outcomes between the groups, thereby providing reliable evidence on the impact of the AI-driven intervention. The randomization process involves a computer-generated sequence, ensuring an unbiased assignment of participants into the intervention group (*n* = 25) and the control group (*n* = 25). Stratification is conducted based on key variables such as age, gender, and specific mental health diagnoses to maintain comparable groups. This methodology is critical for mitigating potential confounding factors and ensuring the validity of the study results. In the intervention group, each participant receives a personalized exercise prescription tailored by the AI system, based on their unique health profile. This approach aims to maximize the efficacy of the exercise regimen in improving mental health outcomes. The control group, on the other hand, receives standard care practices, which may include general health advice or standard exercise recommendations. The distinction in treatment between the groups is central to evaluating the added value of the AI-driven exercise prescriptions.

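### The RCT has 40 participants in the abstract and 50 in the Methods, and neither size has adequate power for the stated effect size of 0.5, so the promise of strong evidence does not fit the design

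*Protocol article*

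**What the plan says.** **Size of the RCT.** The abstract (Methods) says that "a randomized controlled trial (RCT) with 40 participants will be conducted". Section 2.1 says that "the second phase of the study will involves an RCT with 50 participants", split as "25 in the experimental group and 25 in the control group". Section 4.1 repeats the two groups as "each consisting of 25 individuals", and section 4.2 again describes 25 participants in each group.

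**Effect size.** Section 2.1 states "In our analysis, we will set the effect size at 0.5" and adds "This value represents a medium effect size". It names no metric, outcome, visit or target power. The 50-person RCT is introduced in the next sentence.

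**Analysis.** Section 4.5 plans two-tailed tests at 0.05. Groups are compared by independent t-tests, or Mann–Whitney tests where data are not normal. It also plans repeated measures or mixed-model ANOVA across the assessment points. Neither is singled out as primary.

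**Strength of evidence.** Of the trial as designed, section 2.1 says that it "ensures that the results are robust and can be attributed specifically to the intervention, thereby providing strong evidence"; the evidence meant is of possible benefit from the AI system. Section 4.1 likewise speaks of a robust comparison and reliable evidence.

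**The concern.** A reader of the abstract and a reader of the Methods are told of trials of different size. That needs correcting whatever one thinks about power.

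The second matter is fit. The article gives a magnitude it regards as substantial, a test, a significance level and a number of participants, and says that the result will be robust and strong. If the number is too small for that magnitude, a real effect of 0.5 could easily yield a non-significant result that is then read as no benefit. With the t-test, any significant result would have to come from an observed difference larger than 0.5, so it would overstate a true effect of that size.

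**Working it through.** **Inputs**

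- Total RCT size: 50, as 25 per arm (2.1, 4.1, 4.2), or 40 (abstract), taken as 20 per arm on an assumed 1:1 split.
- Effect: 0.5 (2.1), read as a standardised mean difference d with SD = 1. This is an assumption; the word medium supports it.
- Test: independent t-test, two-sided, 0.05 (4.5).
- Target power: none stated, so the article has no power figure to reproduce. The 80% and 90% levels below are reference levels only.

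**Step 1. Power of the t-test at d = 0.5.** The statistic follows a noncentral t with 2n − 2 degrees of freedom and noncentrality d × √(n/2).

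- n = 25: 0.5 × √12.5 = 1.768 on 48 df; power 41.0%.
- n = 20: 0.5 × √10 = 1.581 on 38 df; power 33.8%.

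A normal approximation gives 42.4% and 35.2%.

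**Step 2. Precision, which needs no target power.** The 95% CI half-width in SD units is t(0.975, 2n − 2) × √(2/n).

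- n = 25: 2.011 × 0.2828 = 0.569.
- n = 20: 2.024 × 0.3162 = 0.640.

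These are also the smallest observed differences that reach significance. An observed difference of exactly 0.5 SD would give p = 0.083 with 25 per arm and p = 0.122 with 20 per arm.

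**Step 3. What each size can detect, and what 0.5 would require.**

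- Detectable d at 80% power: 0.81 with 25 per arm, 0.91 with 20 per arm.
- d = 0.5 at 80% power: 64 per arm (128 in total). At 90%: 86 per arm (172 in total).

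**Step 4. More efficient analyses, still at d = 0.5 with full retention.** Averaging m = 3 visits with correlation r multiplies the variance by (1 + 2r)/3. At r = 0.5 the factor is 0.667 and the effective d is 0.5/√0.667 = 0.612. Adjusting for baseline with correlation r gives an effective d of 0.5/√(1 − r²).

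| Analysis (correlation assumed) | 25 per arm | 20 per arm |
|---|---|---|
| t-test, one visit | 41.0% | 33.8% |
| Mean of three visits, r = 0.3 | 66.0% | 56.0% |
| Mean of three visits, r = 0.5 | 56.4% | 47.1% |
| Mean of three visits, r = 0.7 | 49.1% | 40.6% |
| Baseline-adjusted, r = 0.5 | 51.6% | 42.9% |
| Baseline-adjusted, r = 0.7 | 67.9% | 57.8% |
| Baseline-adjusted, r = 0.8 | 82.3% | 72.8% |

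Only one cell passes 80%. It needs a baseline correlation of about 0.8 and an adjustment that section 4.5 does not state. Averaging three visits is open only to outcomes measured at all three. In Table 2 the State and Trait Anxiety Inventory, for instance, is scheduled at 6 and 18 months only.

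**The case against.** **The 0.5 may not be the basis of the sample size.** Section 2.1 introduces it as a value for assessing effectiveness and does not derive 50 from it; it could be a benchmark for the effect sizes that section 4.5 says will be calculated. This stands in part. The article contains no power calculation, so none can be called wrong. What remains is that the size does not suit the magnitude the article itself calls substantial.

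**The metric is open.** Read as Cohen's f = 0.5 (d = 1.0), power would be 93% with 25 per arm and 87% with 20, but that is a large effect, against the text's own label. A group-by-time interaction with f = 0.25 and correlation 0.5 over three visits would give 98% and 94%, but that is a different effect, which the article does not state. The ambiguity is a reason to name the metric.

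**The t-test is not the only planned analysis.** True, so the power figures are conditional. A reader might infer that the trial would more likely than not miss a true effect of 0.5. That holds for the t-test but not for every analysis section 4.5 allows: averaging three visits at correlation 0.5 gives 56% with 25 per arm.

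**The evidence claim concerns attribution.** Much of the sentence in 2.1 rests on randomisation, which does support attributing a difference to the intervention. It does not supply precision, and the words robust and strong imply it.

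**The 40 is an isolated slip.** Three sections of the Methods agree on 25 per arm, so this may well be so. The abstract still has to match.

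**Conclusion.** Two things hold. The article states two sizes for the same RCT, 40 and 50. And, reading 0.5 as a standardised mean difference, neither size has adequate power for it: about 41% with 25 per arm and 34% with 20 by the planned two-sided t-test at 0.05, or about 56% and 47% if three visits are averaged at an assumed correlation of 0.5 with nobody lost. The confidence interval half-width of 0.57 SD at 25 per arm exceeds the effect sought. The wording on robustness and strong evidence is therefore not supported by the design.

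Two stronger readings are not supported. A reader might conclude that the trial cannot detect 0.5 at all; 41% is low power, not none. A reader might also fault the article for giving no attrition allowance; a journal article may leave that to the full protocol, and the shortfall is present with no loss at all.

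**What to change.** 1. State one RCT size in the abstract and in sections 2.1, 4.1 and 4.2.
2. In 2.1, name the metric of the 0.5 and the analysis it refers to, with its outcome and visit.
3. Say what the chosen size delivers. For 25 per arm, for example: *with a two-sided t-test at 0.05, the trial has 80% power for a standardised difference of 0.81 and 41% for 0.5.* If a longitudinal analysis is meant, give the corresponding figure with its assumed correlation.
4. In 4.5, commit to reporting between-group differences with 95% confidence intervals.
5. Replace the claims of robust results and strong evidence in 2.1, and of a robust comparison and reliable evidence in 4.1, with wording that matches this precision.

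The cost is wording only. No extra enrolment is asked for. The downside is that the stated aim becomes more modest.
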